#### Withdrawal of patients from the study and use of collected data in emergency situations:

- If the patient refuses to give post hoc consent, he/she will be withdrawn from the study and the data collected so far will not be used for the study purposes.
- If the representative refuses to give proxy consent, the patient will be withdrawn from the study and the data collected so far will no longer be used for the study purposes.
- If a patient dies before it has been possible to obtain a consent or refusal from the representative and in the absence of a statement of wishes, his/her data collected up to the death will be used for study purposes (without oral consent from a next of kin or designated trusted person ; waiver to ClinO Art 16, alinea 2). This would prevent biasing the study validity (a mortality rate of about 30% is anticipated in view of the clinical situation of the recruited patients (see 11.2).

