#### **6.2.1. Randomisation**

Randomization (1:1) will be stratified by center and generated using the web-based secuTrial® software. Briefly, randomization by blocks of 4 (2 rEEG and 2 cEEG) will be set up in the system by the data managers of the CTU Lausanne. Using login and password, the local investigator (or his designee) will randomize patients after the eligibility check and just before the intervention by asking the system to provide him/her with a randomization number and intervention allocation. Randomization lists will be kept at the CTU Lausanne during the trial and transferred to the sponsor-coordinating investigator for interim analysis or at the end.

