### 11.2 Determination of Sample Size

According to the only available study broadly addressing this issue , patients with consciousness disorders and cEEG have a 25% mortality (corresponding to 75% survival rate) and patients without cEEG a 39% mortality (implying a 61% survival rate). Considering a power of 0.8, an alpha error of 0.05, and applying a 2-sided test, 2x174 patients (348 in total) would be needed to detect a difference of 61% versus 75% in survival ( $\chi^2$  test for independent samples, Stata version 12, College station, TX). This represents a reasonable difference of non-debatable clinical relevance.

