### 11.4 Planned Analyses

#### Analysis of the outcomes

All analyses will be carried out by a professional statistician. At study completion, the two interventional groups will be compared regarding survival at six months as "intention to monitor" (predefined analysis for the primary endpoint) and "per protocol", adjusted for potential confounders (logistic regressions).

Analysis of each secondary endpoint will be also conducted using univariate and multivariate approaches.

For univariate approaches, frequency tables ( $\chi^2$  or Fisher exact tests, as needed), t-test, Mann-Whitney U, and Kaplan-Meier tests will be applied, as needed.

For the multivariate approaches, stepwise logistic regression models will be performed to identify independent outcome predictors among those found to have a  $p < 0.1$  on univariate analyses. Accordingly, risk-prediction models will be set-up and "Goodness-of-fit" of these models will be evaluated using a Hosmer-Lemeshow test to ensure the quality of calibration. Solid predictors will be used to predict survival and functional outcome at six months in a model. To evaluate the performance of these models, sensitivity, specificity, positive predictive value, negative predictive value, unweighted accuracy (using exact binomial 95% CI), area under the Receiver Operating Characteristic (ROC) curve, and reclassification analysis (Net Reclassification Improvement – NRI) will be calculated .

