#### Quantitative EEG analysis

Modern concepts about the neurophysiological basis of unimpaired consciousness propose that a stable balance between functional segregation and integration has to be maintained . Deviations from this physiological state may cause impairment of consciousness and can be quantitatively assessed by studying functional networks derived from EEG signals  as previously done for example for peri-seizure recordings . We will use methods of symbolic analysis  and information theory  to detect pathologic states of hypersegregation or hyperintegration, and to assess the redundancy of single signals and the synchrony between all the EEG signals, in order to detect states of pathologic hypersegregation or hyperintegration. Specifically, we will use the slope cross correlation  as a linear, and horizontal visibility graphs  as a non-linear measure to compute a weighted adjacency matrix consisting of all the pairwise interdependences between EEG signals. From these matrices, we will derive maximal spanning trees , which are uniquely defined acyclic subgraphs that allow to efficiently characterize – by computing their diameter and so-called leafs - the integrative and segregative characteristics of the underlying functional brain networks. We will compare these modern measures of network topology to classical univariate characteristics, such as the relative delta power averaged across all EEG signals. All the necessary algorithms have already been programmed and tested in Matlab by one of the principal investigators ([name]) and are ready for use.

Repetitive routine EEG will only provide sparse temporal information about the evolution of these

network characteristics. Continuous EEG on the other hand should allow to precisely monitor the speed, variability and consistency of these changes. We hypothesize that the faster and the more robust the above described EEG network measures will re-attain a balanced state of integration and segregation, the better the patients' outcome will be. These measures and their dynamics, which reflect neuronal activity, both on smaller and larger spatial scales, will then be correlated with clinical outcomes and tested for their predictive value through multivariate analysis approaches.

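### The prediction models of section 11.4 are chosen by the data and then scored with no optimism correction named, so as written their performance figures are biased upward.

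*Protocol*

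**What the plan says.** Protocol section 11.4, under Analysis of the outcomes, sets out a sequence for prediction. Variables are tested one at a time, those with p<0.1 go into stepwise logistic regression, and the predictors that hold up form models for survival and functional outcome at six months. A Hosmer-Lemeshow test is meant to secure calibration. Performance follows: "To evaluate the performance of these models, sensitivity, specificity, positive predictive value, negative predictive value, unweighted accuracy (using exact binomial 95% CI", then the area under the ROC curve and "reclassification analysis (Net Reclassification Improvement".

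Under Quantitative EEG analysis, the network measures and their dynamics are to be related to outcome and "tested for their predictive value through multivariate analysis approaches". That part gives neither the number of measures nor a selection rule.

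Sections 6.1 and 7.2 describe a single cohort of 350 patients. No hold-out sample, cross-validation, bootstrap, shrinkage or external cohort is named. Where the protocol speaks of validation, it means data entry and cleaning (section 12.2) or published scales and nomenclature.

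**The concern.** If predictors are picked because they fit an outcome, and the model is then scored against that same outcome, chance associations count as performance. AUC, accuracy and NRI are then too high on average. The exact binomial interval treats the model and its cut-off as fixed beforehand, so it reflects neither selection nor fitting. A goodness-of-fit test on the fitting data cannot show that calibration will hold in new patients.

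At stake are the prediction claims. The prognostic role of quantitative EEG is part of the objective in the Study Synopsis and is listed in section 5.2. If the EEG measures go through the same steps, some of their apparent added value could be noise.

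**Working it through.** **1. The plan's own figure.** Section 11.2 states "Considering a power of 0.8, an alpha error of 0.05, and applying a 2-sided test, 2x174 patients (348 in total) would be needed" for 61% against 75% survival. With the pooled-variance formula and no continuity correction:

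n = [1.960·√(2·0.68·0.32) + 0.842·√(0.61·0.39 + 0.75·0.25)]² / 0.14² = (1.293 + 0.549)² / 0.0196 ≈ 173.1, rounded up to 174 per arm.

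Power at 174 per arm is 80.2%, so the stated size reproduces.

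**2. Events for a survival model.** From the section 11.2 rates, 174·0.25 + 174·0.39 = 43.5 + 67.9 ≈ 111 deaths. Section 2.7 says "a mortality rate of about 30% is anticipated in view of the clinical situation of the recruited patients", which gives 0.30·350 = 105. So 105 to 111 deaths are shared among all candidate predictors: about 10.5 to 11.1 per candidate with 10 candidates, and 2.6 to 2.8 with 40.

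**3. What has to be assumed.** The protocol gives no number of candidates, no stay level and no cut-off rule. Assumed here: 10, 20 or 40 independent, normally distributed candidates; 32% deaths (the mean of 25% and 39%); screening at p<0.1; backward elimination at a stay level of 0.05.

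**4. Simulation.** Models were built on n=348 in 200 to 300 replicates. Each was scored on its own patients and on 10,000 new ones. Log-odds coefficients per standard deviation were 0.5, 0.4 and 0.3 (moderate) or 1.0, 0.8 and 0.5 (strong). The NRI is category-free and compares the selected model with a model holding the only true predictor (0.5); it counts as 0 when no noise variable is retained. In the strong and NRI scenarios and for fixed cut-off coverage, the first true predictor was kept in the model.

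| Mean in same patients / in new patients | 10 candidates | 20 | 40 |
|---|---|---|---|
| AUC, no true predictor | 0.538 / 0.500 | 0.557 / 0.500 | 0.603 / 0.500 |
| AUC, three moderate predictors | 0.691 / 0.666 | 0.696 / 0.661 | 0.711 / 0.648 |
| AUC, three strong predictors | 0.808 / 0.794 | 0.807 / 0.789 | 0.815 / 0.784 |
| NRI over the only true predictor | 0.084 / 0.004 | 0.162 / 0.006 | 0.276 / 0.010 |
| Coverage of exact 95% interval for accuracy, cut-off fixed at 0.5 | 89–94% | 89–91% | 79–83% |
| Same, cut-off chosen on the data (Youden), moderate predictors | 77% | 67% | 42% |

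The AUC excess is 0.01–0.04 with 10 candidates, 0.02–0.06 with 20 and 0.03–0.10 with 40. A stay level of 0.10 in the moderate scenario widens it slightly: 0.704 against 0.661 with 20 candidates and 0.715 against 0.646 with 40.

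**5. Cross-check.** With K noise candidates and a stay level of 0.05, the chance of keeping at least one is about 1 − 0.95^K: 40%, 64% and 87% for K = 10, 20 and 40. The simulation gave 43%, 62% and 87%.

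**The case against.** The strongest reply is that much of this rests on silence. Section 11.4 does not say that the models are scored on the patients who built them, and a statistical analysis plan not shown here could add internal validation. That stands as a limit on wording. But the protocol fixes both the selection rule and the performance measures, and it describes no other patients, so apparent performance is what the text yields if followed.

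Second, the link to quantitative EEG is an inference. That part of section 11.4 names no screen, AUC or NRI, and the work has its own team (section 11.4.3) and database (section 12.2.4). This also stands: the concern reaches the EEG measures only if they are assessed with the same steps.

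Third, the candidate set could be small. The text names tree diameter and leaves from two matrices plus relative delta power, about 2·2 + 1 = 5 before any measure of dynamics. A simulation of one real clinical predictor plus noise EEG measures gave a mean apparent AUC gain of only 0.004 with 5 and 0.007 with 10; no noise measure was kept in 78% and 63% of trials. A reader might infer that noise will always look prognostic. These figures do not support that.

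A reader might also infer a larger bias from modelling the cEEG arm alone (n=174). The simulated gap is indeed larger there (0.704 against 0.629 with 20 candidates and moderate predictors). But the protocol states no such analysis, and its French summary says that both cEEG and rEEG traces are used.

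**Conclusion.** The point holds in a limited form. The protocol fixes a data-driven selection and a list of performance measures without optimism correction. As written, these measures are biased upward, the exact binomial interval falls short of its nominal coverage, and the Hosmer-Lemeshow test cannot ensure calibration in new patients. The direction follows from the procedure and appeared in every scenario. The size depends on the number of candidates, the stay level and the cut-off rule, none of which is given; with 10 candidates and strong predictors the AUC excess is only about 0.014.

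A reader might infer that the trial's main result is compromised. It is not: the randomized comparison of mortality and the sample size do not depend on these models. This should be corrected before database lock, but it concerns secondary prediction claims only.

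**What to change.** Repeat the whole process (univariate screen, stepwise selection and any choice of cut-off) within each bootstrap resample or cross-validation fold. Report optimism-corrected AUC, calibration slope and intercept, and classification measures, with resampled intervals in place of the exact binomial one.

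Judge the added value of quantitative EEG by the optimism-corrected change in AUC, not by in-sample NRI. Use a likelihood-ratio test only for a set of EEG measures fixed before the outcome data are seen. On measures selected in the same data it repeats the fault: by 1 − 0.95^K, false positives reach about 23% with 5 noise candidates and 40% with 10 (22% and 37% in simulation).

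The cost is slightly more analysis code and less favourable reported performance. No patients, visits or data items are added.

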#### Quantitative EEG analysis

Modern concepts about the neurophysiological basis of unimpaired consciousness propose that a stable balance between functional segregation and integration has to be maintained . Deviations from this physiological state may cause impairment of consciousness and can be quantitatively assessed by studying functional networks derived from EEG signals  as previously done for example for peri-seizure recordings . We will use methods of symbolic analysis  and information theory  to detect pathologic states of hypersegregation or hyperintegration, and to assess the redundancy of single signals and the synchrony between all the EEG signals, in order to detect states of pathologic hypersegregation or hyperintegration. Specifically, we will use the slope cross correlation  as a linear, and horizontal visibility graphs  as a non-linear measure to compute a weighted adjacency matrix consisting of all the pairwise interdependences between EEG signals. From these matrices, we will derive maximal spanning trees , which are uniquely defined acyclic subgraphs that allow to efficiently characterize – by computing their diameter and so-called leafs - the integrative and segregative characteristics of the underlying functional brain networks. We will compare these modern measures of network topology to classical univariate characteristics, such as the relative delta power averaged across all EEG signals. All the necessary algorithms have already been programmed and tested in Matlab by one of the principal investigators ([name]) and are ready for use.

Repetitive routine EEG will only provide sparse temporal information about the evolution of these

network characteristics. Continuous EEG on the other hand should allow to precisely monitor the speed, variability and consistency of these changes. We hypothesize that the faster and the more robust the above described EEG network measures will re-attain a balanced state of integration and segregation, the better the patients' outcome will be. These measures and their dynamics, which reflect neuronal activity, both on smaller and larger spatial scales, will then be correlated with clinical outcomes and tested for their predictive value through multivariate analysis approaches.

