### **5.2 Secondary Outcomes**

- Functional outcome at four weeks and at six months (evaluated using the modified Rankin Scale (mRS), and the Cerebral Performance Categories (CPC) , ordinal),
- Evaluation at 4 weeks and 6 months of the ability to go back to work/school if previously working/at school (proportion),
- Seizure/SE detection rate, and time to detection after the start of EEG recording, and presence of concomitant clinical signs of seizures (proportion, resp. continuous variable)
- Detection of interictal potentially epileptiform features (spikes, spike and waves, sharp waves, isolated or repeated at <3Hz without any evolution; lateralized rhythmic delta activity  (proportion),
- Rate of in-hospital infections requiring antibiotic treatment at 4 weeks after first EEG (proportion),
- Need and duration of mechanical ventilation at 4 weeks after first EEG (proportion, resp. continuous variable),
- Duration if ICU and hospital stay (continuous variable),
- Patient destination after acute facility (home, rehab, nursing home, other; categorical)
- Change in clinical patient management (i.e., antiepileptic drugs (AED) introduced or stopped, AED increased or decreased, brain imaging procedure order) occurring during the 60 hours following the start of the first EEG (categorical).
- Correlation between quantitative EEG analysis and outcome.

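### The screen-then-stepwise rule in section 11.4 does not keep a network measure's starting level in the model that tests its dynamics

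*Protocol*

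**What the plan says.** The quantitative EEG part of section 11.4 contrasts the two recording modes. Two routine EEGs give little information over time, whereas continuous EEG "should allow to precisely monitor the speed, variability and consistency of these changes". It then states one directional hypothesis: outcome will be better "the faster and the more robust the above described EEG network measures will re-attain a balanced state" of integration and segregation. The next sentence names the predictors, "These measures and their dynamics, which reflect neuronal activity", which will be correlated with clinical outcomes and "tested for their predictive value through multivariate analysis approaches".

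The selection rule stands under Analysis of the outcomes in the same section. Each secondary endpoint gets univariate and multivariate analysis, and for the latter "stepwise logistic regression models will be performed to identify independent outcome predictors among those found to have a" p < 0.1 in the univariate tests. Section 5.2 lists "Correlation between quantitative EEG analysis and outcome" as its last secondary outcome, so the rule covers it. The protocol gives no other rule for choosing terms in these models.

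**The concern.** How far a measure can move towards balance, and how long that takes, both depend on where it starts. The rule judges each candidate alone before any joint model is fitted, and nothing in it holds the starting level beside the dynamic term.

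- **Speed as a rate of change.** A patient balanced at the first recording has a speed near zero, and so has one who stays unbalanced. Large speeds are possible only from poor starts. The association of speed with outcome can therefore nearly cancel when speed is looked at alone. The screen then removes speed before it meets the variable that would reveal its effect.
- **Speed as time to balance.** Patients who start nearer to balance reach it sooner. A univariate correlation can then show that faster is better even when recovery itself has no bearing on outcome.

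At stake is the reading of the dynamic hypothesis, which the section presents as the added information from continuous recording. A false null would hide a real effect of recovery. A spurious positive would credit dynamics with what the first recording already shows.

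**Working it through.** **The plan's own figure.** The protocol gives no calculation for the quantitative EEG hypothesis. Its one sample size (section 11.2) reproduces. With survival 0.61 and 0.75, two-sided alpha 0.05 and power 0.80, n per arm = [1.960·√(2·0.68·0.32) + 0.842·√(0.61·0.39 + 0.75·0.25)]² / 0.14² = (1.293 + 0.549)² / 0.0196 ≈ 173.1, that is 174 (power 0.802). It serves here only as the number of cEEG patients.

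**Inputs.** From the protocol: n = 174; mortality 25% in the cEEG arm; p < 0.1 screen, then stepwise. Mortality 32% is the mean of the protocol's 25% and 39%. Assumed:
- starting distance from balance d0: uniform, half-normal or lognormal (log-SD 0.5);
- recovered fraction f: uniform on 0–1 and independent of d0;
- effect size: log-odds of death 0.8 per SD of the driving variable.

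**Rate-of-change coding.** Let speed s = d0·f and remaining distance r = d0·(1 − f) = d0 − s, with death driven by r. At a fixed d0, a larger s always means a smaller r, so speed is protective. Taken alone, speed is related to r only through

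Cov(s, r) = E[d0²]·E[f(1 − f)] − E[d0]²·E[f]·E[1 − f] = E[d0²]/6 − E[d0]²/4,

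and s and r have the same variance, E[d0²]/3 − E[d0]²/4. Hence:

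| Start | E[d0²] | E[d0]² | Covariance | Variance | Correlation of s and r |
|---|---|---|---|---|---|
| Uniform 0–1 | 0.333 | 0.250 | −0.007 | 0.049 | −0.14 |
| Half-normal | 1.000 | 0.637 | +0.008 | 0.174 | +0.04 |
| Lognormal | 1.649 | 1.284 | −0.046 | 0.229 | −0.20 |

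Speed alone is thus a weak proxy for what drives death, and for half-normal starts the sign is even slightly wrong. In simulation, with the starting level also a candidate:

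| Quantity | Share of trials |
|---|---|
| Speed passes the p < 0.1 screen (chance is 10%) | 11–14%; about 30% with lognormal starts |
| Full rule detects speed | 7–22% |
| Speed detected with the starting level forced in | 90–96% |
| Remaining distance, tested directly, is significant | 97–100% |

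The upper end of 7–22% belongs to lognormal starts, and further runs put it as high as 25%.

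**Time-to-balance coding.** Let t = d0/rate, with rates lognormal (log-SD 0.3, assumed) and death driven by d0 only. Every patient is taken to reach balance. Any effect of t beyond d0 is then spurious.

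| Test of t | Significant at 0.05 |
|---|---|
| Univariate | 94–99% (82–96% in a further set of runs) |
| After the screen and stepwise selection | 12–17% |
| With the starting level forced in | 4–7% |

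**A different model as a check.** Take survival 70%, half-normal starts, speed as absolute improvement per hour, and 174 patients. If only the starting level matters (log-odds 0.5 to 1.0 per unit), speed alone is significant in 34–83% of runs, with faster appearing worse. With the level in the model this is 4–5%. If recovery has a real effect (log-odds 0.4) and the level effect is 0.5, speed is detected in 7% of runs alone and 45% with the level. If the level effect is 1.0, speed alone is significant in 42% of runs, with a mean coefficient of the wrong sign.

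**The case against.** The strongest reply is that the protocol never says speed is tested by itself. It names levels and dynamics together as predictors in multivariate models. A reader might infer from the wording of the hypothesis that the starting level is left out, but the text does not say so, and that stronger reading fails. What remains is narrower: being a candidate does not keep a term in the model, and the screen can remove speed before any joint model exists.

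A second reply is that stepwise selection repairs most of the time-to-balance problem. When the starting level drives outcome, it passes the screen almost always and displaces time to balance in most trials. This stands. The residue is 12–17% instead of about 5%, together with an uncorrected univariate correlation.

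A third is that prognostic information is not lost under rate-of-change coding, because the level at the end of recording still predicts death. This also stands. What is missed is the hypothesis about dynamics, which is the one the protocol states.

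A reader might also infer that patients balanced from the start are necessarily pooled with those who never recover. That follows only if speed is coded as a change or slope. Under time to balance the first group sits at time zero and the second never arrives, so they separate. The protocol fixes neither coding.

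Finally, the definition of speed and the covariate list may belong in a statistical analysis plan that is not shown, and a separate team does this analysis (section 11.4.3). That is fair for the definitions, and no fault is found with them here. The screen and the stepwise step, however, are written into the protocol and can be judged as written.

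**Conclusion.** The point holds in limited form. The stated selection rule does not protect the starting level in models of EEG dynamics, and so it tests the dynamic hypothesis poorly under either natural coding of speed. Under rate-of-change coding the main risk is a missed effect. Under time to balance it is a univariate correlation that mainly reflects initial severity, which the stepwise step corrects mostly but not fully.

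The percentages are illustrative. They rest on assumed starting distributions, recovery independent of initial severity, and an assumed effect size; only the 174 patients, the two mortality levels and the rule come from the protocol. The size of the loss varies with the shape of the starting distribution. The gain from keeping the level in the model appeared in every setting where outcome depended on the starting level or on the distance remaining.

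This is the last-listed secondary outcome, so it should not be called a key hypothesis of the trial. The randomised comparison of 6-month mortality does not depend on it.

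**What to change.** Add to section 11.4, for the quantitative EEG analysis:

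- Every model testing the speed, variability or consistency of a network measure contains that measure's level at the first study recording as a forced term.
- The pair (starting level and dynamic term) is exempt from the p < 0.1 screen and from stepwise removal.
- The dynamic term is judged by a likelihood-ratio test against the model with the starting level alone.
- Any univariate correlation of a dynamic measure with outcome is reported as descriptive.

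The cost is a few lines of protocol or analysis-plan text and one extra term per model. The first recording already exists for each patient analysed, so no new data and no additional patients are needed.
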